## Abstract

**Background:**

Painful cervical radiculopathy can lead to substantial and long-lasting limitations in activities and participation. Surgery is considered when conservative treatment fails to deliver relevant improvements or when neurological signs are severe. However, personalised multimodal physiotherapy may offer non-inferior outcomes to surgery, with possibly fewer adverse events and lower costs. Further research is needed to assess the (cost-)effectiveness of personalised multimodal physiotherapy compared to surgery.

**Methods:**

This randomised non-inferiority study compares personalised multimodal physiotherapy to anterior cervical discectomy with fusion (1:1 allocation ratio) among 126 patients with painful cervical radiculopathy having an indication for surgery, recruited by neurologists. Personalised multimodal physiotherapy uses a mechanism-based approach within a biopsychosocial framework and is tailored to the individual patient. The primary outcome is disability over 12 months using the neck disability index with a prespecified non-inferiority margin of three points. Secondary outcomes include arm and neck pain, fear of movement, and complications. Outcomes are measured at baseline and at three, six, nine, and 12 month follow-up. Additionally, a process evaluation and cost-effectiveness analysis will be performed. Data will be analysed according to the ‘intention-to-treat’ and the 'per-protocol' principle. Both will be conducted using linear and logistic mixed models.

**Ethics and dissemination:**

The study is approved by the medical ethics committee Brabant (P2327).

**Study registration number and status:**

The study protocol is registered at Open Science Framework (ID:S7HWA; registered June 27th, 2023). Recruitment commenced in May 2024. All data are anticipated to be collected by July 2027 when data analysis and interpretation will commence.

## Background

1

Painful cervical radiculopathy (CR) is a form of specific neck pain, in which a cervical nerve root and/or dorsal root ganglion is mechanically and/or chemically irritated. It is caused by narrowing of the foraminal space due to spondylarthrosis and/or disc herniation [[1], [2], [3]]. Radiculopathy refers to cervical nerve root-related neurological deficits, such as sensory, motor or reflex changes, while radicular pain describes the pain that results from nerve root compression or irritation [4]. Radiculopathy and radicular pain can occur in isolation, but often coexist, which is then referred to as painful CR [4]. Painful CR negatively impacts physical function, social participation and mental health [1,3]. In the Netherlands, around 2800 surgeries for painful CR are performed yearly with direct costs estimated at €30 million annually [5,6]. With even substantially higher indirect costs (e.g. due to productivity loss), painful CR imposes a significant societal burden [5].

The natural and clinical course of painful CR is highly variable [2,7]. Symptoms resolve largely over 4-6 months, and ∼80% of patients recover within 24-36 months [8,9]. However, if conservative management does not lead to meaningful improvements, patients are usually referred to a neurologist and invasive treatments are considered, such as epidural steroid injections and/or surgery [10,11]. Anterior Cervical Discectomy with Fusion (ACDF) is the most common surgical approach for people with painful CR and is generally considered effective at reducing arm pain [12]. Although surgery provides faster pain relief than conservative management, the long-term effect of personalised multimodal physiotherapy may be comparable [[13], [14], [15]] and total costs may be lower. Also, the potential adverse events associated with ACDF surgery are avoided with conservative management.

Personalised multimodal physiotherapy integrates interventions proven to reverse pathophysiological mechanisms linked to entrapment neuropathies [[16], [17], [18]]. The pathophysiology of painful CR remains not fully understood [19], but involves a complex interplay of peripheral and central mechanisms. The interactions between these mechanisms and the impact of psychosocial factors underscore the importance of addressing both peripheral and central mechanisms, as well as psychosocial factors, in the treatment of painful CR. Physiotherapy that targets these mechanisms has shown effectiveness in reducing pain and disability [[16], [17], [18]], especially when tailored to individual needs [20]. A recent systematic review revealed that improvements in pain and disability following personalised multimodal physiotherapy were comparable to surgery for people with painful CR at 12 months follow-up [14]. However, this review only included two relatively small studies, and the certainty of the evidence was low. Furthermore, no cost-effectiveness studies have been conducted. Therefore, based on the assumed comparable effectiveness [14], fewer and less severe adverse-events and lower costs associated with personalised multimodal physiotherapy, we will conduct a non-inferiority study to assess the (cost-)effectiveness and process of implementation of personalised multimodal physiotherapy compared with ACDF surgery for people with painful CR. We hypothesise that personalised multimodal physiotherapy is non-inferior to ACDF surgery, with fewer and less severe adverse-events, and is associated with lower healthcare and societal costs. This paper describes the study design and outlines the content of personalised multimodal physiotherapy.

## Methods and design

2

### Study design

2.1

This is a pragmatic multicentre non-inferiority randomised clinical trial (RCT) with parallel economic and process evaluation. To describe the treatment The Standard Protocol Items: Recommendations for Interventional Trials (SPIRIT) statement [21] will be followed and the Template for Intervention Description and Replication (TIDier) checklist is used [22].

### Study population

2.2

Patients with painful CR with an indication for surgery and no contra-indication for physiotherapy are eligible to participate. The diagnosis of painful CR requires two criteria: (1) a clinical presentation indicative of painful CR and (2) relevant corresponding findings on MRI (e.g., disc herniation and/or spondylosis). The clinical presentation consists of radicular pain (i.e., pain due to irritation of a cervical nerve root or dorsal root ganglion [14]) with typically more intense arm pain than neck pain [23], and at least one of the following: paraesthesia, numbness, muscle weakness, and/or reduced reflexes [1,2,24]. Additional inclusion criteria are age ≥18, and at least eight weeks of unilateral arm pain with an intensity of ≥4 on a 0-10 Numeric Rating Scale (NRS). Exclusion criteria are cervical myelopathy, motor deficits measured with the Medical Research Council (MRC) scale for muscle strength ≤3, previous neck surgery, contra-indication for surgery, inability to perform physical activity [25], current self-reported psychiatric disorders, rheumatic disease (rheumatoid arthritis, spondylitis ankylopoetica, Forestier's disease), malignancies causing CR-like complaints, or pregnancy.

### Procedure

2.3

#### Screening phase

2.3.1

Potential participants are informed about the study by neurologists from 11 secondary care hospitals and clinics, who diagnoses painful CR. A neurosurgeon verifies whether there is an ACDF surgery indication. Patients who are eligible and provide written informed consent will be scheduled for baseline measurements. Baseline questionnaires are filled in by the participants, and physical tests are conducted by a clinical investigator ([name]). In Fig. 1 the study flow and different study phases are shown.

**Fig. 1 fig1:**
[figure not shown]
Flowchart of the different study phases. Abbreviations: ACDF: Anterior cervical discectomy with fusion.

#### Randomisation and blinding

2.3.2

After baseline measurement, an in independent researcher randomly allocates participants via a phone call to personalised multimodal physiotherapy or surgery with a 1:1 allocation ratio using concealed, computer-generated block randomisation (block sizes of four or six) [26]. Due to the nature of the study, blinding of patients and health care providers is not feasible. However, the clinical investigators and the statistician conducting the analyses are blinded.

#### Treatment phase

2.3.3

In the treatment phase, the physiotherapy group receives personalised multimodal physiotherapy. In case of progressive neurological deficits, or a substantial increase in arm pain or paraesthesia, participants are referred back to the neurologist for further assessment, at which point a (delayed) ACDF surgery could be decided. The surgery group receives the ACDF surgery conform usual care.

#### Follow-up time-points

2.3.4

Follow-up assessments will take place at three, six, and 12 months. To reduce the risk of recall bias in cost reporting, an additional cost evaluation will be conducted at nine months. Participants who have not completed the follow-up questionnaire will receive reminders on days five and eight. If responses are still missing after two weeks, a follow-up phone call will be made to encourage adherence to the study.

### Treatment

2.4

#### Personalised multimodal physiotherapy

2.4.1

Personalised multimodal physiotherapy is a tailored mechanism-based treatment approach that combines multiple interventions based on the individual needs, symptoms, and goals of each patient within a biopsychosocial model [20]. The overall aims of this treatment are to restore function, enhance the patient's ability to manage their condition independently, and reduce pain.

Based on current knowledge of working mechanisms, the interventions used within personalised multimodal physiotherapy are divided into two categories: treatments with a predominantly peripheral or central mechanistic effect, while acknowledging that various interventions (e.g., exercise) influence both pain mechanisms [[27], [28], [29]]. Peripheral pain mechanisms include changes in ectopic nerve impulses (e.g. reducing local neuroinflammation [30,31]) and changes in nociceptor activity (e.g. muscle spasm). Central pain mechanisms occur within the spinal cord or brain and include central processing of nociceptive signals and the modulation of descending inhibitory and facilitatory activity. Selecting interventions that specifically address the underlying physiology of a particular pain mechanism may enhance the effectiveness of physiotherapy [18]. Table A1 (Appendix) provides an overview of pain mechanisms and suggested interventions.

Over a period of eight to 12 weeks, the physiotherapy will take place without a set number of treatment sessions. Personalised multimodal physiotherapy is delivered in live, one-on-one sessions within the existing care structure at the physiotherapists' clinics. The baseline measurement results are compiled into a visual diagram (see Figure A1), which is shared with the treating physiotherapists and forms the basis for selecting the intervention. During the intake session, the physiotherapist and patient collaboratively establish treatment goals through shared decision-making. Adjustments to the treatment plan are made in subsequent sessions when necessary.

Some participants may experience mild side effects following physiotherapy, such as neck discomfort, muscle stiffness, fatigue, increased muscle tension, or flare-up of symptoms. These rarely last longer than 24 h [32]. There are no reported severe side effects of the proposed physiotherapy treatment [7,[16], [17], [18],^33^].

##### Participating physiotherapists

2.4.1.1

Physiotherapists who hold a master's degree in musculoskeletal physiotherapy are eligible to deliver the physiotherapy treatment. During a one-day training, working mechanisms of interventions are explained, techniques are practiced, case-based training is provided to enhance practical decision-making skills and a manual is distributed describing relevant theory. Due to the personalised nature of the treatment, physiotherapists use their clinical expertise to determine the appropriate frequency and duration, rather than following a fixed schedule and personalise interventions within protocol guidelines. A guideline for therapy intensity is the resolution of treatment-related pain and/or symptom exacerbation within 24-36 h. Physiotherapists are instructed to monitor each individual treatment session and document the details of the interventions provided. Quality assurance is maintained through regular communication with physiotherapists and evaluation of their adherence to the protocol. Additionally, physiotherapists can seek expert guidance from two professionals of the research team ([name]) who have over ten years of relevant experience.

#### ACDF surgery

2.4.2

ACDF surgery is performed by experienced neurosurgeons in participating hospitals, conform usual care. In summary, after general anaesthesia the surgeon makes a small transverse skin incision at the left or right side of the neck, according to the preference of the surgeon [34,35]. Medial to the carotid sheath, the pre-vertebral space is opened and the anterior cervical spine is exposed. The correct index level is verified with fluoroscopy. Caspar spreader and two distraction pins are placed in the affected segment. Care will be taken not to damage the adjacent level discs. A standard anterior discectomy with the aid of loupe magnification or microscope (depending on the surgeon's preference) is performed. The posterior longitudinal ligament is opened and the nerve root and dura are decompressed adequately. Once the anterior discectomy has been performed, the endplates are prepared for fusion. According to the preference of the surgeon, a solid titanium cage or polyetheretherketone interbody cage (filled with local bone obtained from removed osteophytes) is placed within the intervertebral disc space under fluoroscopic guidance. Depending on the surgeon's preference and patient characteristics an anterior fixation plate can be placed to secure the cage. If required, a vacuum drain is placed and the wound is closed in layers.

Most hospitals have a follow-up six to nine weeks after surgery [10,35] and recommend performing minimal home exercises, taking pain medication (e.g., paracetamol [35]), and following lifestyle guidelines. Post-operative physiotherapy is not advised during recovery [10].

A systematic review reported adverse events for ACDF ranging from 13.2 to 19.3% in the United States [36]. The most frequent complication was transient dysphagia [36]. However, studies conducted in the Netherlands indicate that complication rates are lower, ranging from 0 to 16% [37,38].

#### Cross-over

2.4.3

The participant and physiotherapist will evaluate the effectiveness of the treatment, based on persistence of symptoms. If deemed unsuccessful or in case of progressive increase of symptoms, a delayed ACDF surgery remains an option and can be initiated at any time during the follow-up period of the study. Also, if complaints are in remission, ACDF surgery can be cancelled. Due to the pragmatic study design, co-interventions are allowed in both treatment arms.

### Outcome measures

2.5

Patients complete online surveys using Qualtrics to collect data (Qualtrics, Amsterdam, The Netherlands; www.qualtrics.com). All physical tests are performed in-person by the clinical investigators. An overview of timing of data collection and measuring tools is provided in Table 1.

**Table 1 tbl1:** Overview and timing of measurements and measuring tools.

Domain	Questionnaire	T0	T1	T2	T3	T4
Disability in people with neck pain	Neck Disability Index (NDI)	x	x	x	-	x
Pain intensity	Numeric Rating Scale (NRS) for arm and neck pain	x	x	x	-	x
Perceived recovery	Global Perceived Effect (GPE)	-	x	x	-	x
Quality of life	EuroQol 5 Dimension 5 Level (EQ-5D-5L)	x	x	x	-	x
Symptoms and limitations	Cervical Radicular Impact Scale (CRIS)	x	x	x	-	x
Activity limitations	Patient Specific Functional Scale (PSFS 2.0)	x	x	x	-	x
Patient acceptable symptom state	Patient Acceptable Symptom State (PASS)	x	x	x	-	x
Fear of Movement	Tampa Scale of Kinesiophobia (TSK)	x	x	x	-	x
Pain catastrophizing	Pain Catastrophizing Scale (PCS)	x	x	x	-	x
Knowledge of pain neurophysiology	Neurophysiology of pain test	x	x	-	-	-
Economic evaluation	Cost questionnaire	x	x	x	x	x
Sociodemographic and clinical data	Custom-made questionnaire	x	x	x	x	x

**Domain**	**Physical test**					

Cervical range of motion	Left and right rotation	x	-	-	-	x
Muscle strength	Kenn muscles C5-Th1	x	-	-	-	x
	C5: m. deltoideus					
	C6: m. biceps brachii					
	C7: m. triceps brachii caput longum					
	C8: m. adductor pollicis					
	Th1: mm. interossei palmaris and dorsalis					
	Th2: n.a.					
Nerve mechano-sensitivity	ULNT 1 (median), 2B (radial) and 3 (ulnar)					
Sensibility (light touch)	Soft brush C5-Th2	x	-	-	-	x
Sensibility (nociception)	Pinwheel C5-Th2					
Reflex	Biceps and triceps tendon reflex	x	-	-	-	x
Pain modulation (facilitation)	Temporal Summation of Pain (C6 and TA)	x	-	-	-	x

Abbreviations: ULNT: Upper Limb Neurodynamic Test, TA: tibialis anterior. Details about the scores and clinimetric properties are presented in Table A2 (Appendix). T0: baseline, T1: 3 months, T2: 6 months, T3: 9 months, T4: 12 months.

#### Primary outcomes

2.5.1

The primary outcome is disability over 12 months, measured with the Neck Disability Index (NDI) [39], which assesses self-reported pain intensity and limitations of activities in daily life. The Dutch version of the NDI is a valid and responsive measure of disability [40].

#### Secondary outcomes

2.5.2

The secondary outcomes are arm and neck pain intensity (NRS), perceived recovery (GPE) [40], quality of life (EQ-5D-5L) [41], symptoms and limitations (CRIS) [42], patient-specific activity limitations (PSFS 2.0) [43], patient acceptable symptom state (PASS) [44], fear of movement (TSK) [45], pain catastrophising (PCS) [46], knowledge of pain mechanisms (neurophysiology of pain test) [47], return-to-work (days), medication use, healthcare and societal costs (cost questionnaire), percentage of cross-overs, treatment adherence, (re)surgeries and complications.

### Sample size and non-inferiority margin

2.6

A sample size of 126 participants is needed to achieve a power of 0.80 to test the hypothesis that personalised multimodal physiotherapy is non-inferior to ACDF surgery, with a standard deviation of six points on the NDI, an alpha of 2.5%, and allowing for a drop-out rate of up to 20% [48,49].

To determine the non-inferiority margin, we calculated the Smallest Worthwhile Effect (SWE) for the Neck Disability Index (NDI). The SWE represents the minimum clinical benefit required to justify a treatment, accounting for its specific risks, costs, and burdens [50,51]. While a 20% between-group difference is typically recommended for conservative treatments [50], this threshold is often increased by 10% for chronic conditions [52].

In consultation with our patient representative, we set the SWE at 30%. Given that the Minimal Clinically Important Change (MCIC) for patients undergoing surgery for cervical radiculopathy is nine points on the NDI [53], the 30% threshold translates to 3 points non-inferiority margin. Consequently, physiotherapy is considered non-inferior to surgery if the difference in NDI improvement between the two groups is less than three points.

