#### Statistical analysis

2.9.1

First, normality of the data will be checked by the Kolmogorov-Smirnov test and visual inspection of Q-Q plots, box plots, and histograms. If needed, data will be transformed to obtain normal residuals. The primary analysis will be conducted according to the intention-to-treat principle, with secondary analyses performed based on the per-protocol approach. A one-sided alpha of 2.5% will be used. For the primary and secondary outcomes, linear mixed models will assess between-group differences in outcome measures over 12 months. To analyse the over-time effect, the fixed part of the model will include the outcome measure over time, treatment group, and baseline outcome correction (when applicable). A random intercept will be selected to account for the correlated nature of multiple measurements from the same participant. Potential confounders will be included as covariates in the adjusted model. To assess the differences in treatment effect at each time point, we will include an interaction term between time and treatment group. The regression coefficient (B), p-value, and confidence intervals (95% CI) will be computed for the crude models (only corrected for the baseline value of the outcome) and the confounder-adjusted models.

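### The 126 patients contain no drop-out allowance at the stated alpha: with 20% loss, the stated inputs give about 71% power, not 80%

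*Protocol article*

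**What the plan says.** Section 2.6 (Sample size and non-inferiority margin) of the protocol article makes the claim in one sentence: "A sample size of 126 participants is needed to achieve a power of 0.80", "with a standard deviation of six points on the NDI, an alpha of 2.5%, and allowing for a drop-out rate of up to 20" per cent. The same section derives the margin: "the 30% threshold translates to 3 points non-inferiority margin". Section 2.9.1 (Statistical analysis) fixes the sidedness: "A one-sided alpha of 2.5% will be used". Section 2.3.2 gives 1:1 allocation, and the Abstract repeats 126 as the number of patients in the trial.

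Section 2.6 gives no true difference, no correlation between measurements, no gain from baseline adjustment and no repeated-measures basis. It does not say whether the SD of 6 refers to a single visit, a change score or an already adjusted value.

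**The concern.** The sentence in section 2.6 says that 126 both delivers 80% power and already absorbs a loss of up to 20%. The stated SD, margin and alpha lead to exactly 126 with no loss at all, so the drop-out allowance appears never to have been applied.

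Power against drop-out is the main design property claimed for this trial. In a non-inferiority trial, too little power shows up as a confidence interval that crosses the margin. A reader who trusts the stated 80% may take such a result as evidence against physiotherapy, when on the plan's own inputs the chance of missing true non-inferiority was nearer 29% than 20%.

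**Working it through.** **Inputs**

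- Total sample size 126, or 63 per arm (section 2.6; 1:1 allocation from section 2.3.2)
- Power 0.80, SD 6, margin 3, drop-out up to 20% (section 2.6)
- Alpha 2.5% (section 2.6), one-sided (section 2.9.1)
- True difference 0. This is an assumption. No value is stated, but the Background bases the non-inferiority design on the two treatments being about equally effective.

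**Step 1: reproduce the plan's figure**

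n per arm = 2 × (z₀.₉₇₅ + z₀.₈₀)² × SD² / margin² = 2 × (1.960 + 0.842)² × 36 / 9 = 62.8, rounded up to 63. The total is 126, with power 0.801 at 63 per arm. This matches the stated number exactly, but it is the number of evaluable patients.

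**Step 2: add the stated drop-out**

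63 / (1 − 0.20) = 78.75, rounded up to 79 per arm, or 158 in total. The cruder inflation 63 × 1.20 = 75.6, rounded up to 76 per arm, gives 152. Neither is 126.

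**Step 3: power with 126 randomised and 20% lost**

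- Evaluable per arm: 63 × 0.80 = 50.4
- Standard error: 6 × √(2 / 50.4) = 1.195
- Power: Φ(3 / 1.195 − 1.960) = 0.709 by the normal approximation, and 0.700 by the noncentral t distribution
- Type II error: about 29%, against the planned 20%

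**Step 4: look for another reading that gives 126**

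| Reading | Total before drop-out | Total after 20% drop-out |
|---|---|---|
| One-sided 2.5%, margin 3 (as stated) | 126 | 158 |
| 2.5% taken as two-sided (1.25% one-sided) | 154 | 194 |
| One-sided 2.5%, unrounded margin 0.30 × 9 = 2.7 | 156 | 196 |
| One-sided 5%, margin 3 | 100 | 126 |

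Of these, only the last row reaches 126 after drop-out: 2 × (1.645 + 0.842)² × 36 / 9 = 49.5, so 50 per arm, and 50 / 0.80 = 62.5, so 63 per arm. It needs an alpha that the article does not state. The article does not show whether the inflation was left out or the calculation was run at one-sided 5%. In both cases, power at the alpha to be used in the analysis is about 71% on the stated inputs.

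**Step 5: what the planned model could recover**

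Section 2.9.1 plans a baseline-adjusted linear mixed model, and Table 1 shows the NDI at 3, 6 and 12 months. Suppose SD 6 is the single-visit SD, the correlation between follow-ups is ρ and the correlation of baseline with each follow-up is r. The variance of the average over three visits is then multiplied by (1 + 2ρ)/3 − r². None of these correlations is in the article, so the following are assumptions:

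- ρ = 0.8, r = 0.3: factor 0.867 − 0.090 = 0.777, power at 50.4 per arm about 0.81
- ρ = 0.5, r = 0.5: factor 0.667 − 0.250 = 0.417, power about 0.97

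The factor needed to restore 80% power is 50.4 / 62.8 = 0.80.

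**The case against.** The strongest reply is that the two-sample formula is not the planned analysis. At 50.4 per arm, a variance factor of about 0.80 restores 80% power. At a single visit, a baseline correlation of about 0.44 is enough for that (1 − 0.44² ≈ 0.81), and repeated follow-ups would lower the requirement. The 71% is also the lower end in two respects. It applies at the full 20% loss (at 10% loss, 56.7 per arm, power is 0.76), and it treats drop-outs as contributing nothing, whereas section 2.9.2 plans a likelihood-based analysis that uses their 3- and 6-month data. A small true advantage for physiotherapy would help as well. Finally, the article is condensed and the sources behind its calculation are not shown.

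Most of this is fair, and it limits the conclusion: the trial has not been shown to lack 80% power under its planned model. It does not repair section 2.6. That section states inputs and a result that disagree, which is different from leaving a detail to the full protocol. It invokes no variance reduction, and the exact match of 126 to the plain two-sample result suggests that none was used. If SD 6 is already an adjusted value, the gain in step 5 would be smaller or absent. The assumed true difference of zero is not harsh either: a true 1-point disadvantage for physiotherapy would give Φ(2 / 1.195 − 1.960), or about 0.39, at 50.4 per arm.

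**Conclusion.** The concern holds. At the stated one-sided alpha of 2.5%, with SD 6 and margin 3, 126 is the evaluable number for 80% power and leaves nothing for drop-out. With 20% loss, power is about 71% (70% by the t distribution), and 158 would have to be randomised to deliver what section 2.6 claims.

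This rests on a true difference of zero, a simple two-group comparison and no information from patients who drop out. Actual power under the planned mixed model may be 80% or more, but that depends on correlations the article does not give. The error is in the stated justification. The article does not show whether it arose from an omitted inflation or from a calculation at one-sided 5%.

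**What to change.** Correct section 2.6 in one of two ways:

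- **(a)** State that 126 is the number of evaluable patients for 80% power, and that with 20% drop-out the stated inputs give about 71%.
- **(b)** Replace the calculation with one for the planned analysis, the baseline-adjusted linear mixed model over 3, 6 and 12 months. Say what the SD of 6 refers to, give the assumed follow-up and baseline correlations, and report power for 126 randomised with 20% drop-out. The correlations should come from prior data, not be chosen so that 126 works.

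In either case, check the sponsor's calculation and confirm that it was run at the one-sided 2.5% used in the analysis.

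The cost is one paragraph in the protocol, carried into the SAP. The stated power becomes less favourable or is properly justified, and recruitment is unchanged. The Abstract anticipates that data collection will end by July 2027, so the correction can be made before the analysis. Delivering 80% power at 20% drop-out through sample size alone would take 32 more patients (158 − 126), but the correction does not depend on that.

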#### Non-inferiority evaluation

2.9.2

Differences between the study-arms with 95% confidence interval and p-values will be calculated for the crude and adjusted models based on potential differences in patient characteristics with a non-inferiority margin of three points on the NDI over 12 months. Missing data and reasons for drop-outs will be reported. Linear/logistic mixed models handle missing data more flexibly due to its reliance on maximum likelihood estimation, which allows for the incorporation of missing values under missing at random assumptions.

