## Discussion

3

This paper describes the protocol for a non-inferiority randomised clinical trial that will assess the (cost-)effectiveness of personalised multimodal physiotherapy compared to ACDF surgery over a 12-month period in patients with painful CR who have an indication for surgery. We hypothesise that personalised multimodal physiotherapy is non-inferior to ACDF surgery in patients with painful CR based on disability over one year.

There is a strong need for studies investigating the effectiveness of personalised multimodal physiotherapy [14]. To our knowledge, this is the first study that simultaneously investigates the effectiveness and cost-effectiveness of personalised multimodal physiotherapy compared to surgery in patients with painful CR who have an indication for surgery. The personalised multimodal physiotherapy treatment is unique and carefully developed based on prior research into the effectiveness of the interventions for painful CR [[60], [61], [62]]. We believe the design of this study allows to assess whether the proposed treatment is a feasible alternative to ACDF surgery, which is the golden standard for painful CR and generally regarded as effective in reducing pain associated with this condition [12,13,[63], [64], [65]]. The non-inferiority design allows for flexibility in the treatment choice for people with painful CR, by demonstrating that personalised multimodal physiotherapy might be comparable effective on disability whilst offering additional benefits that might align better with individual preferences.

Besides the strengths, the proposed study has some potential limitations. The use of a non-inferiority margin is inherently prone to discussion. When comparing conservative treatment to no-treatment, the between-group difference should be at least 20% [50]. In this study, however, we compare conservative treatment to surgical treatment. As surgery is an invasive treatment associated with higher risks for (serious) adverse events, and based on the smallest worthwhile effect for chronic sciatica complaints [52], we increased the threshold to 30%. This results in a non-inferiority margin of 3 points on the NDI. Further, the use of the NDI as primary outcome measure doesn't take into account the radicular arm pain, which is one of the most important symptoms people with painful CR experience [12,23].

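### The 3-point non-inferiority margin does not follow from its stated derivation: 30% of a nine-point MCIC is 2.7 points, and 3 points is one third

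*Protocol article*

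**What the plan says.** Section 2.6 (Sample size and non-inferiority margin) builds the margin in three steps.

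- It fixes the smallest worthwhile effect (SWE) as a percentage: "In consultation with our patient representative, we set the SWE at 30" per cent.
- It takes the MCIC, which "for patients undergoing surgery for cervical radiculopathy is nine points on the NDI".
- It combines the two: "the 30% threshold translates to 3 points non-inferiority margin".

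The decision rule follows. Physiotherapy counts as non-inferior "if the difference in NDI improvement between the two groups is less than three points". Section 2.9.2 (Non-inferiority evaluation) carries the same value into the analysis, "with a non-inferiority margin of three points on the NDI over 12 months", with a 95% confidence interval, and the Abstract calls the margin prespecified. The Discussion (section 3) restates the derivation: "we increased the threshold to 30%. This results in a non-inferiority margin of 3 points on the NDI".

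The article nowhere gives the value 2.7, mentions rounding, or says that a third of the MCIC was intended.

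**The concern.** The article states both inputs and the result, and they disagree. This is not detail that a fuller protocol or an analysis plan could supply, because no other document can make 30% of nine equal three.

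The discrepancy sits in the threshold that decides the primary conclusion, and a wider margin is easier to meet. The comparison is between a model-estimated mean difference, with its confidence limit, and the margin. Both are continuous, so whole-point scoring of the NDI does not force a whole-point margin. A reader who accepts 30% as the clinical justification would therefore be shown a non-inferiority claim that allows a loss of up to one third of the MCIC.

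**Working it through.** **Inputs from the article.** SWE 30%, MCIC 9 points, margin 3 points, SD 6, power 0.80, N = 126 and drop-out up to 20% (section 2.6); one-sided alpha 2.5% (section 2.9.1); 1:1 allocation (section 2.3.2).

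**Assumptions.** The true difference is 0; the article gives no figure, only an expectation of comparable effectiveness. The standard error is that of a simple two-sample comparison. Non-inferiority is declared when the upper limit of the 95% interval for the physiotherapy deficit lies below the margin.

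**Step 1: the margin.**
- 0.30 × 9 = 2.7 points.
- 3 / 9 = 33.3% of the MCIC.
- Excess: 3 − 2.7 = 0.3 points; 0.3 / 2.7 = 11%.
- For 30% to give 3 points, the MCIC would have to be 3 / 0.30 = 10 points, not nine.

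**Step 2: the article's own sample size.**
- n per arm = 2 × [(1.960 + 0.842) × 6 / 3]² = 62.8, so 63 per arm and 126 in total.
- This matches the stated N before any drop-out. The design is therefore built on 3 points. How the 20% drop-out allowance enters N is a separate matter and is not relied on here.

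**Step 3: the same design at 2.7 points.**
- n per arm = 2 × [(1.960 + 0.842) × 6 / 2.7]² = 77.5, so 78 per arm and 156 evaluable. With 20% drop-out, 156 / 0.80 = 195 randomised.

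**Step 4: power at a true difference of 0.**
- With 63 evaluable per arm, SE = 6 × √(2/63) = 1.069.
- Margin 3: Φ(3/1.069 − 1.960) = 0.80.
- Margin 2.7: Φ(2.7/1.069 − 1.960) = 0.71.
- With about 50 evaluable per arm (126 less roughly 20%), SE = 1.20, and power is 0.705 at margin 3 and 0.614 at margin 2.7.
- In both settings the margin alone accounts for about 9 percentage points.

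**Step 5: what the 3-point rule lets through.**
- Largest observed deficit that still passes with 63 per arm: 3 − 1.960 × 1.069 = 0.90 points, against 2.7 − 1.960 × 1.069 = 0.60 points.
- If the true deficit were exactly 2.7, the chance of passing the 3-point rule is Φ(0.3/1.069 − 1.960) = 4.7% with 63 per arm (4.4% with 50 per arm). A 2.7-point rule would hold it at 2.5%.

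**The case against.** The strongest reply is that the rule itself is not in doubt. Three points appears consistently in the Abstract, section 2.6, section 2.9.2 and the Discussion, and N = 126 is built on it. The slip is then in the explanatory sentence, and 30% may simply be a loose way of saying one third. This much stands: nobody could misapply the rule. It also means a reader should not infer that 2.7 is the true margin, or that a result between 2.7 and 3.0 would breach the loss the plan accepts. Section 2.6 states the acceptable difference outright as less than three points. What can be said is that such a result would exceed 30% of the MCIC, which is the only justification offered.

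A second reply is that the derivation is not precise to one decimal. The percentage comes from a customary 20% plus a customary increase, and the nine-point MCIC may itself be rounded. But if the MCIC lay anywhere from 8.5 to 9.5, 30% of it would run from 2.55 to 2.85, always below 3. Rounding to a whole point may be what happened, but the article does not say so. It would also be an inference that the value was raised in order to make success easier. The documents show the direction of the gap, not a motive.

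Third, the power figures are illustrative only. Section 2.9.1 specifies a baseline-adjusted repeated-measures mixed model, whose standard error may differ. It would also be wrong to attribute a fall to about 0.61 to the margin, because power with about 50 per arm is already 0.705 at 3 points. The rest of that fall comes from drop-out. None of this changes 2.7 against 3.

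**Conclusion.** The stated derivation gives 2.7 points, and the trial uses 3. The margin is one third of the MCIC, 0.3 points (11%) wider than the 30% that section 2.6 and the Discussion cite, and the gap favours physiotherapy. That finding is arithmetic on the article's own figures and needs no further assumption.

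The consequences are modest but fall on the primary conclusion: power of 0.80 against 0.71, and a pass rate of about 4.7% instead of 2.5% at a true deficit of 2.7. These rest on SD 6, one-sided 2.5%, 63 evaluable per arm and a simple two-sample standard error; the power figures also assume a true difference of 0.

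The article shows that the justification and the margin disagree. It does not show that 3 points is clinically indefensible. It also does not show which margin the registry holds, since it gives only the registration number and date; prespecified is the supportable word.

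**What to change.** Keep the prespecified 3-point margin and make three changes.

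1. In section 2.6 and in the Discussion, state that 3 points is one third (33%) of the nine-point MCIC, and remove the claim that it results from 30%.
2. Justify one third in its own right. The reasons now given (chronicity in section 2.6; the invasiveness and risk of surgery and the sciatica threshold in the Discussion) are offered for 30%.
3. Prespecify reporting whether the upper confidence limit also lies below 2.7 points (30% of the MCIC), so that readers can see whether the conclusion depends on the gap.

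This costs a few sentences, a slightly less favourable justification and one extra reported comparison. It can be done before data collection ends, which the article anticipates by July 2027.

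If the sponsor holds to 30% instead, the margin is 2.7 and the stated power must be restated as lower. That is more than a wording change in a trial that has recruited since May 2024. On the inputs above it means either about 0.71 power with 126 evaluable, or 156 evaluable (195 randomised with 20% drop-out) for 0.80.
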